### Intervention allocation

The experimental unit for this study will be a single patient episode (rather than the patient) identified by an event ID, since one patient can have two or more separate episodes of focal *status epilepticus* over the course of the study. Participant event/episode IDs will be randomly assigned to groups in a 1:1 ratio using block randomisation (6 blocks) by the sealed envelope software [26]. Based on the event ID the dedicated team member will be able to infer the study arm that determines the device setup for the first two days, i.e. active (early start) vs. sham (delayed start).

TDCS device marked as #1 will be set up individually for each experimental event for day 1 & 2 to either sham or active treatment with the aid of a special tool and instructional video. A second device marked as #2 will permanently be set up for active treatment and used for the remaining sessions (3 up to 14). One member of the team, not involved in the delivery of tDCS or data analysis, will be responsible for the randomization process, and sham/active device assignment and delivery. The random group assignment will be kept secret in a password protected file only accessible to the responsible team member. All remaining team members and all participants and relatives will be unaware to which treatment arm the participant is assigned. A record will be kept confirming when and by whom the randomisation code was requested and provided.

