## Statistical methods

### Statistical analyses

The data will be tabulated using descriptive statistics. Mean and standard deviation will be reported for continuous data. Median and range will also be reported for skewed data. Categorical data will be described using percentages and frequencies.

The primary analysis of the binary outcome of a 50% reduction in epilepsy frequency (number and duration of seizures, jerks/min) from baseline (counted on day 0) will be completed by applying a generalised estimating equation to thus obtain robust standard errors and test whether the tDCS group improves more rapidly than the sham group.

Further analysis will consider a more complex model incorporating random slopes where appropriate. Sensitivity analysis for missing data will also be investigated. Other outcome data will be analysed as appropriate using a mixed effects model for continuous data and a generalised estimating equation for binary, categorical or count data with appropriate distribution and link function.

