#### Target difference and sample size

Assuming a minimum of one assessment per patient event per day, each event will contribute 14 data points over 14 days of treatment (tDCS or sham). Further assuming no association between days of treatment and reduction in epilepsy events, the outcome data are treated as clustered data for the purposes of the power calculation. Assuming 5% type I error, 90% power, and 10% intra-patient correlation, 28 patient events will be required over 14 days of treatment to detect an improvement of 20% in events that achieved 50% reduction in seizure frequency. The sample size calculation also assumes that only 10% of the events in the placebo group will achieve 50% reduction in epilepsy frequency from baseline (on day 0). To account for drop-out, 30 patient events will be required for this study. The patient events will be allocated equally to active and sham tDCS groups. These calculations were determined based on clinical significance, patient perspectives, historical data, statistical considerations, and regulatory guidelines [25].

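### The stated 90% power holds only for a 14-day average of daily responses, not for the share of events that respond or for the planned test of faster improvement

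*Protocol article*

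**What the plan says.** All places are in the protocol article.

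- **Target difference and sample size** words both effect inputs as shares of events. The aim is "to detect an improvement of 20% in events that achieved 50% reduction in seizure frequency", and the control assumption is that "only 10% of the events in the placebo group will achieve 50% reduction in epilepsy frequency from baseline".
- The same paragraph builds the calculation on daily results: "each event will contribute 14 data points over 14 days of treatment". It continues: "Further assuming no association between days of treatment and reduction in epilepsy events, the outcome data are treated as clustered data". The result is: "Assuming 5% type I error, 90% power, and 10% intra-patient correlation, 28 patient events will be required over 14 days of treatment". The total is then raised to 30 for drop-out.
- **Intervention allocation** says: "The experimental unit for this study will be a single patient episode (rather than the patient) identified by an event ID".
- **Aims, objectives, and outcomes** defines the endpoint as a reduction of more than 50% from day 0, assessed by daily reporting. It gives no day, window or rule for combining the daily results.
- **Statistical analyses** applies a generalised estimating equation (GEE) to "The primary analysis of the binary outcome of a 50% reduction in epilepsy frequency". The hypothesis there concerns speed: whether the tDCS group gets better faster than the sham group.
- **Randomization and intervention protocol** gives sham on days 1 and 2 only. From day 3 both arms receive active stimulation.

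**The concern.** The power statement and the calculation behind it use different units. A reader of the sample-size paragraph would take it that the trial has a 90% chance of showing 30% against 10% of events responding. The calculation counts 14 daily results per event and spreads the 10% and 30% over those days.

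The analysis section adds a third quantity, the speed of improvement. A sizing that assumes response does not depend on day cannot speak to that.

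At stake is what the 90% can be cited for. If the deciding result is one yes/no per event, or a difference in speed, the trial has no valid power statement. A difference in daily proportions could also be reported afterwards as a share of events that responded.

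**Working it through.** **Inputs (Target difference and sample size).** p1 = 0.10, p2 = 0.30, α = 0.05, power 0.90, intra-patient correlation (ICC) 0.10, m = 14 results per event, equal allocation. Sidedness is not stated; two-sided is the choice that reproduces 28.

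**1. Reproducing the plan's figure**

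Independent observations per arm (pooled two-proportion formula):

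n = [z(0.975)·√(2·p̄·(1−p̄)) + z(0.90)·√(p1(1−p1) + p2(1−p2))]² / (p2−p1)², with p̄ = 0.20

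= [1.960 × √0.32 + 1.282 × √0.30]² / 0.04 = 81.96, rounded up to 82.

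Design effect = 1 + (14 − 1) × 0.10 = 2.3.

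Events per arm = 82 × 2.3 / 14 = 13.47, so 14 per arm and **28 in total**, an exact match.

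Other variants do not match: 32 with continuity correction, 26 with unpooled variance or arcsine, and 22 or 24 one-sided, depending on rounding.

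**2. Power for the quantity actually sized (event-days, 14 days, ICC 0.10)**

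Effective observations per arm are 14 × 14 / 2.3 = 85.2, or 15 × 14 / 2.3 = 91.3. Power is 91% with 28 events and 93% with 30. With 14 events per arm it falls to 61% at ICC 0.3, 44% at 0.5 and 25.5% at 1.0, where the 14 results collapse to one.

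**3. Power if 10% and 30% are one result per event (two-sided 5%)**

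| Events per arm | Normal approximation | Pearson chi-square, exact power | Fisher |
|---|---|---|---|
| 14 | 25.5% | 25.1% | 13.7% |
| 15 | 27.1% | 27.8% | 14.9% |

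On this reading 90% power would need 82 events per arm, 164 in total.

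**4. Power for event-days within the sham-controlled window (m = 2)**

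Design effect = 1 + 1 × 0.10 = 1.1. Effective observations per arm are 14 × 2 / 1.1 = 25.5, or 15 × 2 / 1.1 = 27.3.

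| ICC | 14 per arm | 15 per arm |
|---|---|---|
| 0.10 | 43% | 45% |
| 0.3 | 37% | 39% |
| 0.5 | 33% | 35% |

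**5. Averaging over all 14 days under the actual design**

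Suppose, as an assumption for illustration, that both arms respond at 30% per day from day 3. The average difference is then 0.20 × 2/14 = 0.029, and power is about 6% with 28 or 30 events. Relabelling the inputs as event-days while keeping all 14 days and the 90% would therefore not repair the statement.

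**6. The speed hypothesis**

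No power can be computed for it. The protocol gives no time course for either arm, and the sizing assumes that day has no effect.

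**The case against.** The best defence is that the paragraph is consistent once read as a whole. It opens by setting up daily data. If day has no effect, the share of events in response on any given day equals the share of event-days in response, and that is the marginal proportion a GEE estimates. Making the episode the experimental unit says what is randomised, not how many outcomes each unit yields. No section proposes a test on one result per event, so 14% to 28% is the power of an analysis that the protocol does not plan. The statistical analysis plan, which the Blinding section says is finalised before unblinding, may fix the contrast.

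Much of this stands. The 28 is not a calculation error, and the low power is conditional on the per-event reading. What does not stand is the power sentence. The given-day reading is possible but not stated, and the words about events that achieve a reduction naturally suggest one outcome per event. The defence also relies on there being no day effect, whereas the analysis section sets out to test speed. A later analysis plan can choose the contrast, but it cannot make the 90% apply to a quantity that was not sized.

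A reader might go further, construct responder definitions such as any day, most days or the last day, and argue that the trial's verdict would flip between them. The protocol proposes none of these, so that argument has no basis in it.

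**Conclusion.** The point holds as a mismatch between the power claim and its basis. The 90% is valid for a time-averaged event-day difference of 10% against 30% over 14 days, at ICC 0.10 and with no day effect (91% with 28 events, 93% with 30). It is not valid for a share of events that respond, where power is 14% to 28%, and it has no bearing on the test of faster improvement.

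Two stronger readings should be resisted. One is that the sample size was miscalculated; it reproduces exactly. The other is that the trial's power simply is 14% to 28%; that figure requires one result per event, which the planned GEE on daily data does not clearly imply.

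The figures assume two-sided 5% testing, the protocol's own rates and, for daily data, its ICC unless another value is shown.

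**What to change.** In Aims, objectives, and outcomes, in Statistical analyses, and in Target difference and sample size:

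1. Name one deciding contrast and its time window, consistent with sham being given on days 1 and 2 only. If speed of improvement is to decide, define it and size it with a stated time course for each arm.
2. Word the 10% and 30% in the unit of that contrast, either event-days or events.
3. Replace the 90% with the power that the planned 30 events give for that contrast. Allowing for 28 to 30 evaluable events, this is about 43% to 45% for event-days on days 1 and 2 at ICC 0.10 (lower at higher ICC), or about 14% to 28% for one result per event.
4. Label any other responder summary as descriptive.

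The cost is wording and a restated power basis, with no extra patients or data. The downside is a less favourable stated power.

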#### Oversight and monitoring

##### Composition of the coordinating centre and study steering committee

As part of the pre-study risk assessment the ethics committee identified that a study steering committee is not required for this non-CTIMP clinical study of a CE marked device for an off-label indication.

##### Composition of the data monitoring committee, its role and reporting structure

No formal data monitoring committee will be convened. This study is classed as non-CTIMP and the ethics committee approved that the study treatment is not predicted to cause high morbidity or mortality or is not associated with unknown or uncertain risks. Instead, interim safety and efficacy will be reviewed on a regular basis. An annual progress report will be submitted each year to the REC by the CI until the end of the study. This report will be submitted within 30 days of the anniversary date on which the original favourable ethical opinion was granted.

### Adverse event (AE) reporting and harms

AE reporting will be restricted to adverse events occurring during or resulting from the study intervention (tDCS) or study assessments. Such adverse events will be documented in the participant medical records recording causality and severity and will also be recorded on the study adverse event log held in the Investigator site file. AEs will be followed up until resolution or until stabilisation (if complete resolution is not anticipated). Any other adverse events/serious adverse events that occur will not be reported as AEs, including any events occurring during or related to the participant’s inpatient hospital stay. In the event of a Serious Adverse Event (SAE), the sponsor, The Newcastle upon Tyne Hospitals NHS Foundation Trust will be notified immediately by email (within 24 h of site awareness of the event). If complete information is not available or if a PI/Investigator cannot be obtained within 24 h, the SAE report should be submitted as incomplete in the first instance and the missing details provided at the earliest opportunity. SAEs will be followed up until resolution or until stabilisation (if complete resolution is not anticipated) and updated reports should be provided to the sponsor as required until resolution. All SAEs will be recorded in the participant medical notes and recorded on the study adverse event log held in the Investigator Site File (ISF)/ Trial Master File (TMF). Any SAE notification emails, including updated notifications, will be retained in the ISF and TMF. Any SAEs that are related to the study intervention/assessments and that are classified as unexpected will be reported to the Research Ethics Committee (REC) by the Sponsor and reported to other Sponsor departments as per Sponsor procedures. Any abnormal results or issues of concern identified during any study visit or during the analysis of the study samples will be documented and referred to the Principal Investigator for discussion with the participant’s routine clinical care team to decide about (dis-)continuation of the treatment.

### Frequency and plans for auditing study conduct

The study is monitored and audited by the sponsor. The CI will notify the REC of any adverse events or the early termination or end of study in accordance with the required timelines.

Any change to this protocol after approval has been given will be notified as an amendment to relevant parties.

## Discussion

### Study design, practical and operational challenges

Refractory focal epilepsy associated with a mitochondrial disorder, while rare, often has a poor prognosis. Here, we address the unique challenges encountered in designing a randomized, sham-controlled study within the context of rare diseases.

First, designing this randomised sham-controlled study has posed ethical challenges of administering a treatment to one group and not another while keeping high methodological stringency. Our team’s prior treatment of five patients with mitochondrial epilepsy, who had received cathodal tDCS on compassionate grounds, suggests that focal episodes may resolve within the first three days of stimulation [27]. Based on that, we adopted a delayed-start design. One group receives the treatment immediately (early-start), while the delayed-start group receives a non-active (sham) treatment for the first two days and then receives active treatment from day 3.

Secondly, recruiting patients with a condition classified as a rare disease who experience an acute event is logistically challenging and, in this case, requires active recruitment methods. Potential participants will be identified by their health care provider while patients are admitted to the hospital for an acute focal epileptic event that remains unresolved by antiepileptic drugs. Consequently, the timeframe of recruitment is unpredictable, and to complete recruitment within the 3-year study period, individual means of recruitment may be considered.

Third, for some participants admission to our premises could be disruptive e.g., if their symptoms can be managed externally. To not exclude any potential participants from entering the study, we consider remote treatment for those patients. In that case patients would be referred to our site for their tDCS treatment. After initial supervised device training, tDCS will be self-applied by patients at home or in their care setting, under the remote supervision of a medical professional. Depending on the participants’ circumstances, we will determine individually which option is least disruptive.

Fourth, patients exhibit various types of seizures, each requiring unique methods of recording and diagnosis. To ensure optimal daily monitoring of seizure activity, we maintain close monitoring of the patient, provide flexible seizure diary templates, and record relative values.

### General discussion and conclusions

tDCS is being recognized as a promising non-invasive, non-pharmacological, adjunctive treatment for refractory epilepsy due to its low-risk profile, low cost, and ease of use compared to other surgical neurostimulation techniques such as deep brain stimulation and vagus nerve stimulation [16]. Moreover, in many people with epilepsy, anti-epileptic drugs become less effective over time, leading to seizures that are refractory to medical therapy. Surgical removal of an epileptic focus is an invasive procedure that could potentially be postponed or even avoided by neuromodulation. Several studies involving patients with refractory focal epilepsy have shown evidence supporting the efficacy of tDCS in reducing the frequency of clinical seizures [16–20]. Based on 27 studies, including nine randomized controlled trials, cathodal tDCS was evaluated as safe and likely effective for seizure control in patients with drug-resistant focal epilepsy [28]. However, larger sham-controlled randomized studies are needed to further advance tDCS therapy in the management of epilepsy.

In conclusion, while existing studies provide evidence for the efficacy of tDCS in refractory epilepsy, its effectiveness as an adjunctive treatment in focal refractory epilepsy in mitochondrial disease remains inconclusive. Study findings from this delayed start, double-blind, sham-controlled study showing treatment efficacy would contribute to the development of tDCS as a mainstream treatment option for focal epileptic seizures associated with mitochondrial disease.

## Data Availability

No datasets were generated or analysed during the current study.

## Abbreviations

AE: Adverse Event
CE: Conformité Européenne (‘European conformity’)
CI: Chief Investigator
CRF: Case Report Form
CTIMP: Clinical Trial of Investigational Medicinal Product
DICOM: Digital Imaging and Communications in Medicine
EEG: Electroencephalogram
GCP: Good Clinical Practice
GP: General Practitioner
HRA: Health Research Authority
HTA: Human Tissue Authority
ICH: International Council for Harmonisation of Technical Requirements for Pharmaceuticals for Human Use
ICF: Informed Consent Form
ILAE: International League Against Epilepsy
ISF: Investigator Site File
LTD: Long-Term Depression
MHRA: Medicines & Healthcare Products Regulatory Agency
MRI: Magnetic Resonance Imaging
NHS: National Health Service
NICE: National Institute for Health and Care Excellence
NuTH: Newcastle upon Tyne Hospital Foundation Trust
PI: Principal Investigator
PIS: Participant Information Sheet
R&D: Research & Development
REC: Research Ethics Committee
SAE: Serious Adverse Event
SOP: Standard Operating Procedure
SUSAR: Suspected Unexpected Serious Adverse Reaction
TDCS: Transcranial direct current stimulation
TMF: Trial Master File
UK: United Kingdom
UKCA: UK Conformity Assessed
